#### Pre-intervention period

After the baseline assessment, participants will undergo a 4-week no-intervention period to assess the stability of outcome measures. During this time, they will use the provided iPad to complete daily Ecological Momentary Assessments (EMAs), which will track mental health status and collect additional control measures. EMAs will be administered through the mEMA app (https://ilumivu.com/solutions/ecological-momentary-assessment-app/), with participants receiving daily notifications prompting them to complete a brief survey within a six-hour window (6:00 p.m. to midnight). Two surveys will be administered through the mEMA app during the 4-week pre-intervention period: (1) the first is a daily survey assessing control variables related to the four mechanistic pathways through which enriched environments are thought to promote brain plasticity and recovery: motor, sensory, cognitive, and social stimulation (Vive et al., 2022). This survey uses Likert scales to measure the extent of motor, sensory, cognitive, and social activity throughout the day, as well as music engagement. Specifically, whether participants listened to music outside of scheduled sessions and whether the listening was intentional (see Supplementary Materials). Participants will complete this survey each weekday starting after the baseline session; and (2) the Profile of Mood States (POMS), a 36-item standardized self-report questionnaire that assesses temporary mood states across six subscales: Tension-Anxiety, Depression-Dejection, Anger-Hostility, Vigor-Activity, Fatigue-Inertia, and Confusion-Bewilderment (McNair et al., 1971). The POMS will be administered every three days beginning on the first day of the 4-week period (i.e., days 1, 4, 7, 10, 13, 16, 19, 22, 25 and 28, for a total of 10 data points).

#### Pre-intervention evaluation session

After the 4-week pre-intervention period, participants will complete a pre-intervention evaluation session. In addition to repeating behavioral clinical outcome measures (i.e., mental health and cognitive assessments), this session will include the collection of neural and physiological biomarkers. We will acquire functional and structural MRI data on a 3T Siemens Prisma scanner equipped with a 64-channel phased-array head coil.

##### Neuroanatomical biomarkers.

We will examine biomarkers related to grey and white matter. For grey matter we will collect a high resolution T1 MPRAGE image (TR = 2400 ms, TE = 2.24 ms, flip angle = 8º, voxel size = 0.80 × 0.80 × 0.80 mm^3^, 256 sagittal slices, acq. matrix = 320 × 300). For white matter, we will collect diffusion-weighted images (DW-MRI; one run with ten interleaved non-DW volumes and 128 DW-ones, b-value=1500 s/mm2, 2×2×2 mm^3^).

##### Neural circuits and function.

We will collect fMRI data (sequential whole-brain multi-echo echo-planar imaging volumes; TR = 1500 ms, TE=45 ms, flip angle = 77º, voxel size = 1.5 × 1.5 × 1.5 mm^3^, 64 axial slices, acquisition size = 104×104) while participants listen to self-selected rewarding songs and emotionally neutral music (i.e., elevator music; Abrams et al., 2024) across three runs. Each run will consist of four trials, including two rewarding and two neutral excerpts presented in randomized order. Each excerpt will last 60 seconds, followed by a 30-second rest period. After each excerpt, participants will rate their perceived pleasure and familiarity using a 5-point Likert scale. At the end of the evaluation session, participants will also complete a burden rating.

##### Physiological biomarkers.

Physiological data (electrodermal activity and heart rate) will be acquired concurrently with the neural data while participants listen to music using an MRI-compatible Biopac system.

#### Intentional Music Listening Intervention

Patients will engage in daily one-hour listening sessions over a four-week period (excluding weekends; total: 20 sessions). Each participant will be provided with an iPad equipped with a prepaid SIM card, allowing them to stream music freely without relying on personal internet access. The iPad will come preloaded with Spotify (for music streaming and playlist creation), FaceTime (for video communication with team members), and the mEMA app (for ecological momentary assessments). During the baseline session, a team member will familiarize each participant with the iPad and its key features, including FaceTime, Spotify, and the mEMA app. Team members will then work with participants to co-create a playlist of self-selected, culturally relevant songs. This playlist can be updated at any time by the patient independently or with support from the team. To promote flexibility and adherence, team members will have remote access to participants’ Spotify accounts and may assist with updating or playing music based on the participant’s preferences.

Each daily remote listening session will begin with a team member calling the patient on the iPad at a pre-arranged time. At the beginning of the session, the playlist will be updated according to the patient’s preferences and mood. Patients will then be asked to listen intentionally to the playlist without engaging in other activities (e.g., doing chores). However, participants will be allowed to engage in music-related behaviors during listening, such as singing or moving to the music. The total duration of each session will be one hour, including at least 40 minutes of music listening and up to 20 minutes for setup, preparation, and playlist updates. Team members will remotely monitor the listening sessions and will be available via FaceTime throughout the session to provide support if needed. This will improve adherence to the protocol. To accommodate varying levels of impairment, needs, and technological familiarity, team members will provide as much support as each participant requires, while also encouraging patient agency. Participants will be guided as needed but allowed to manage their listening sessions independently (e.g., by skipping songs on their own). Listening sessions will also be video-recorded to allow for later annotation of music-related behaviors (e.g., dancing). If video monitoring or recording fails due to technical issues, the research team will first attempt to resolve the problem remotely via FaceTime. If the issue cannot be resolved remotely, a team member will visit the participant in person to fix the problem or replace the iPad. If feasible, a make-up session will be conducted on the same day. At the end of each session, the monitoring team member will rate the feasibility of the session (“not feasible” , “partially feasible” or “fully feasible”) and the participant will rate the acceptability of the session (“not acceptable” , “partially acceptable” or “fully acceptable”). Finally, a team member who was not involved in the listening session will review the session’s video recording and score its fidelity as either “delivered according to protocol” or “not delivered according to protocol.”

The same control measures collected during the pre-intervention period will continue to be gathered during the intervention using EMAs via the mEMA app (motor, sensory, cognitive, and social activity; music engagement outside of scheduled sessions; and the POMS).

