**Methods and analysis.:**

We will conduct a parallel group randomized controlled feasibility trial enrolling 60 patients with chronic stroke from a well-characterized stroke registry in New York City. Participants will be randomized to either an intentional music listening (IML) group or an active control group that listens to audiobooks. The study includes a 4-week pre-intervention period during which no treatment is administered; this phase is designed to assess the stability of outcome measures. Following this, participants will engage in 1-hour daily listening sessions over a 4-week intervention period. All listening activity (i.e., track identity, duration, and engagement) will be continuously tracked using custom open-source software, providing a measure of treatment dose. Behavioral outcomes related to mental health will be assessed at baseline, pre-intervention, post-intervention, and 3-month follow-up. Multimodal biomarkers (functional and structural MRI, electrodermal activity, and heart rate) will be collected pre- and post-intervention. The primary objective is to establish feasibility, defined by rates of retention and adherence, treatment fidelity, feasibility, acceptability, and participant burden. Secondary outcomes include recruitment and randomization rates. This trial will provide essential data to inform the design of future large-scale clinical studies of IML for post-stroke mental health recovery.

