#### Control Intervention

The control group will consist of chronic stroke patients who will intentionally listen to audiobooks instead of music. Assessing a group of patients listening to audiobooks will allow us to control any effects unrelated to music (e.g., intentional listening, non-music specific auditory stimulation, social interaction via the phone calls with the team members, etc.). The control group will follow the same protocol as the IML group, ensuring that both groups are matched for treatment intensity. Audiobooks will be played via Spotify and will be self-selected and culturally relevant to each participant, with the option to update selections during the 4-week intervention period. Audiobooks will not contain background music. Importantly, if participants in the control group typically listen to music as part of their daily routine, they will be asked to do so using the Spotify app on the provided iPad. No curated playlists will be created for the control group. This approach will allow, for the first time in an IML intervention, objective tracking of music use in the control condition. After the follow-up evaluation session, control participants will be informed of the potential benefits of IML.

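### The no-treatment run-in is not protected from music exposure: Spotify, and on the natural reading the music-arm playlist, are available from the baseline session, so exposure can differ by arm before the pre-intervention evaluation

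*Protocol article*

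**What the plan says.** **Run-in.** The abstract (Methods and analysis) describes "a 4-week pre-intervention period during which no treatment is administered; this phase is designed to assess the stability of outcome measures". The section Pre-intervention period repeats that "participants will undergo a 4-week no-intervention period to assess the stability of outcome measures". The participant already holds the device in that period: "During this time, they will use the provided iPad to complete daily Ecological Momentary Assessments (EMAs".

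**Device and playlist.** The section Intentional Music Listening Intervention states: "Each participant will be provided with an iPad equipped with a prepaid SIM card, allowing them to stream music freely without relying on personal internet". It then places the introduction to the device at baseline: "During the baseline session, a team member will familiarize each participant with the iPad and its key features, including FaceTime, Spotify, and the mEMA app". The following sentence says that team members will 'then' build the playlist with participants, and after that: "This playlist can be updated at any time by the patient independently or with support from the team".

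**Control arm.** The section Control Intervention states: "No curated playlists will be created for the control group". Controls who habitually listen to music are asked to do so through Spotify on the same iPad.

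**Order of events.** Under Screening, eligible patients are randomized and then scheduled for the baseline session, and experimenters are not blinded to group. Allocation is therefore known to staff when the iPad is introduced.

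**Measurement of music use.** The run-in EMA asks each weekday about music listening and whether it was intentional. The section Tracking Software describes continuous logging, including listening outside scheduled sessions. It does not mention the run-in by name.

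**The concern.** A run-in that is meant to show how outcomes behave without treatment should withhold what is specific to the treatment. Here the stated sequence appears to give music-arm participants the tool and the content of the intervention four weeks before the first session. If some of them play the playlist in those weeks, three things are at stake.

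- **Stability assessment.** Change between baseline and the pre-intervention evaluation would mix natural variation with some response to music, possibly more in one arm.
- **Pre-intervention reference.** Any early response is counted before the reference value, so the pre-to-post change in that arm shrinks. Table 1 shows MRI and physiology only at the pre- and post-intervention evaluations, so no earlier value can stand in for them. The fMRI task uses self-selected rewarding songs and asks for familiarity ratings, so recent extra exposure to favourite music could plausibly matter there.
- **Record of habitual listening.** The run-in EMA would describe music use just after a new, free music source had been supplied, and not usual use.

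**Working it through.** The plan gives no figure to reproduce: the sample size rests on precedent, and run-in listening is not quantified. The check is therefore the order of events, followed by a sizing under stated assumptions.

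**1. Order of events**

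| Step | What is stated | Music arm | Control arm |
|---|---|---|---|
| Randomization | Before the baseline session (Screening) | Allocated | Allocated |
| Baseline session: iPad and Spotify | Explicit | Yes | Yes |
| Baseline session: playlist | By inference from 'then' | Yes, on the natural reading | None curated |
| Run-in, 4 weeks | iPad in use for EMAs; no limit on Spotify or playlist stated | Spotify and playlist | Spotify |
| Pre-intervention evaluation | First MRI and physiology | Reference value | Reference value |
| Intervention, 4 weeks | Supervised sessions | Music | Audiobooks |

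Access to Spotify is explicit and the same in both arms. Early access to the playlist is inferred and concerns the music arm only. Two details support the inference: preferences are collected at baseline expressly for playlist building, and the playlist may be changed without limit of time, whereas updates to audiobook selections are tied to the intervention period.

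**2. Does listening outside sessions count?** The abstract treats all tracked listening as a measure of treatment dose. The Discussion defines dose by the duration and the acoustic content of the music. On the article's own terms, playlist listening in the run-in would resemble dose, although it is not a treatment session.

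**3. Size under assumptions**

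- Sessions: 4 weeks × 5 weekdays = 20. Minimum listening: 20 × 40 min = 800 min.
- Assumed m minutes per weekday over 20 run-in weekdays, as a share of the minimum dose: 20 × m / 800.
  - m = 10: 200 / 800 = 25%
  - m = 20: 400 / 800 = 50%
  - m = 30: 600 / 800 = 75%
- Assumed m minutes on all 28 days: 28 × m / 800.
  - m = 5: 140 / 800 = 17.5%
  - m = 60: 1,680 / 800 = 210%

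The values of m are not in the document. The ratio also treats unsupervised and supervised minutes as equal, and ignores that playlist listening may replace music the person would have played anyway.

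**4. Effect on a pre-to-post contrast.** If a fraction f of a true effect d arises in the music arm before the reference measurement, the observed contrast is d × (1 − f). With an assumed d = 0.5 SD, f = 10%, 25% and 50% give 0.45, 0.375 and 0.25 SD. This shows direction and scale only; neither d nor f is given.

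**The case against.** The strongest reply is that access is not treatment. The intervention consists of a staff call, an instruction to listen attentively without other activities, remote monitoring and video recording, and none of that is scheduled before the pre-intervention evaluation. This stands. A reader might infer that the run-in is in fact a treated period, or that exposure does differ by arm. The documents support neither: both arms have Spotify, and how much anyone listens is unknown.

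The playlist date is also not explicit. The account of the baseline session and Table 1 list only preferences, and the playlist sentence stands under the intervention heading. This stands in part: baseline is the natural reading, but it is a reading.

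The difference between arms also depends on randomization coming before baseline; without that order, a music-arm playlist could not exist at that visit. The point is therefore not wholly separate from the timing of randomization.

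Run-in listening is partly measured, by the EMA and perhaps by the tracker. That detects exposure but does not prevent it, and the article does not say that the tracker covers the run-in.

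The consequence is limited. The primary outcomes are feasibility metrics, the statistical section describes tests of feasibility outcomes, and the Discussion says that the trial is not powered for clinical change. Clinical scores are also taken at baseline, before any run-in listening, so they keep a clean reference. Only MRI and physiology lack one.

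Finally, device settings and participant instructions may be in a fuller document. The absence of a lock is therefore not itself the finding. The finding is the stated sequence, which puts the tool, and apparently the content, in place before a period described as untreated.

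**Conclusion.** The point holds as a risk built into the stated sequence. The run-in is called treatment-free, but it is not protected from the active ingredient, and music exposure before the pre-intervention evaluation can differ by arm. What is affected is the stability assessment and the only pre-treatment MRI and physiology values. The session-based primary benchmarks are little affected.

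Spotify access from baseline is explicit. The difference between arms rests on reading 'then' as the baseline visit. The amount of exposure is unknown, and the percentages above are scenarios, not estimates. The matter deserves correction because the change is nearly free and because a later efficacy trial informed by this protocol could inherit the same order of events.

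**What to change.** - Collect music and audiobook preferences at baseline in both arms, as now. Create and release the music playlist, and the audiobook selection, only after the pre-intervention evaluation: at the end of that visit or at the first listening session. State this timing in the text.
- Keep Spotify live and tracked during the run-in in both arms. Give both arms the same instruction to keep to their usual listening, and state that the tracker covers this period.
- Report tracked and EMA run-in listening by arm as pre-treatment exposure.

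**Cost.** A change of wording, and a short set-up step moved from the baseline visit to the end of the pre-intervention visit or the first session.

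Switching Spotify off during the run-in would be stricter, but it is a real trade-off. It would give up objective tracking of habitual listening and leave only self-report, which the Introduction names as a weakness of earlier studies. It would also not stop participants playing music on their own devices.

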#### Control Intervention

The control group will consist of chronic stroke patients who will intentionally listen to audiobooks instead of music. Assessing a group of patients listening to audiobooks will allow us to control any effects unrelated to music (e.g., intentional listening, non-music specific auditory stimulation, social interaction via the phone calls with the team members, etc.). The control group will follow the same protocol as the IML group, ensuring that both groups are matched for treatment intensity. Audiobooks will be played via Spotify and will be self-selected and culturally relevant to each participant, with the option to update selections during the 4-week intervention period. Audiobooks will not contain background music. Importantly, if participants in the control group typically listen to music as part of their daily routine, they will be asked to do so using the Spotify app on the provided iPad. No curated playlists will be created for the control group. This approach will allow, for the first time in an IML intervention, objective tracking of music use in the control condition. After the follow-up evaluation session, control participants will be informed of the potential benefits of IML.

#### Tracking Software

To track each patient’s music and audiobook listening as objectively and precisely as possible, we developed a Python script that automatically logs the Spotify playback activity of a given account. The script utilizes the Spotify Web API in a while loop, requesting device and playback information from the server in each iteration. After each iteration there is a two-second pause to comply with Spotify rate limits. To track when the Spotify account is opened and closed the script must run continuously, which requires a dedicated computer. We will use the NYU Supercomputer Greene for this purpose. Participants’ music and audiobook listening will be continuously tracked using this custom Python script. Running the script continuously will also allow us to capture music or audiobook listening that occurs outside of the scheduled sessions with equal precision.

The tracking script is initiated by entering the patient’s Spotify account ID, which serves as their unique identifier for monitoring listening activity. It then reads the necessary authentication details from the *patient_ids.json* file to initialize tracking for that patient. Once the account becomes active on any device, the script automatically sends an email notification to a designated account owned by our team indicating that a session has started and begins logging playback and device information in real time. More specifically, the script tracks and stores the following information: patient ID, session start time in EDT, artist name, album name, track name, track’s original duration, starting position of the track in seconds (whether it starts from the beginning or not), session start and end timestamps, track listening duration, total track listening duration (accumulated if the track is repeated), track end reason (end of song, repeated, skipped, seeked forward/backward, paused, or Spotify closed), and the device name that the account was used on (e.g., iPad, MacBook). We use Python’s datetime library to track time and calculate the track start position, track listening duration, total track listening duration, and session duration. This will enable precise calculation of treatment dose.

When the user closes the Spotify app or remains in a paused state for more than five minutes, the session is marked as finalized. Then the script sends an email notification with the total session duration, saves the information as a .csv file in the designated folder for that patient, and uploads it to an encrypted, password protected, Google Drive account. The code for this software can be found here: https://github.com/intentional-music-listening/SpotifyTrackerOpen

#### Acoustic Fingerprinting

With the exact list of music that patients listened to, we will use MIR methods and open-source software (e.g., *librosa*; McFee et al., 2015) to analyze the acoustic and musical features of the music participants listen to daily. Different measures will be extracted, based on previous research showing that specific acoustic properties of music (e.g., tonality, rhythm, timbre, loudness, surprise, amount of vocal vs. instrumental music; Carone and [name], 2024; Groves et al., 2025; Sihvonen et al., 2020, 2021a, 2021b; Salakka et al., 2022; Abrams et al., 2022; Skerritt-Davis & Elhilali, 2018) can affect emotional and reward related responses to music and modulate mental health and cognition (Ding et al., 2023; Parada-Cabaleiro et al., 2022; Bowling, 2023).

For control participants, acoustic fingerprint measures will be extracted from the audiobooks. Using an Audio-to-Text transcriber, we will convert the exact audiobook section each participant listened to into text. From these transcripts, we will compute lexical (e.g., average word frequency, average number of morphemes per word), semantic (e.g., average number of semantic neighbors per word), and syntactic (e.g., number of phrases and nested structures) complexity measures, among others. These analyses will be performed using open-source toolboxes such as the Stanford Parser (Klein & Manning, 2003; Yap et al., 2011).

